## Abstract

**Background:**

Children in Sub-Saharan Africa (SSA) comprise half of the total regional population, yet existing mental health services are severely under-equipped to meet their needs. Although effective interventions for the treatment of disruptive behavioral disorders (DBDs) in youth have been tested in high-poverty and high-stress communities in developed countries, and are relevant for widespread dissemination in low- and middle-income countries (LMICs), most of these evidence-based practices (EBPs) have not been utilized in SSA, a region heavily impacted by poverty, diseases including HIV/AIDS, and violence. Thus, this paper presents a protocol for a scale-up longitudinal experimental study that uses a mixed-methods, hybrid type II, effectiveness implementation design to test the effectiveness of an EBP, called Multiple Family Group (MFG) aimed at improving child behavioral challenges in Uganda while concurrently examining the multi-level factors that influence uptake, implementation, sustainment, and youth outcomes.

**Methods:**

The MFG intervention will be implemented and tested via a longitudinal experimental study conducted across 30 public primary schools located in both semi-urban and rural communities. The schools will be randomly assigned to three study conditions (*n* = 10 per study condition): (1) MFG delivered by trained family peers; (2) MFG delivered by community health workers; or; (3) comparison: usual care comprising mental health care support materials, bolstered with school support materials. A total of 3000 children (ages 8 to 13 years; grades 2 to 7) and their caregivers (*N* = 3000 dyads); 60 parent peers, and 60 community health workers will be recruited. Each study condition will comprise of 1000 child-caregiver dyads. Data will be collected at baseline, 8 and 16 weeks, and 6-month follow-up.

**Discussion:**

This project is the first to test the effectiveness of the MFG intervention while concurrently examining multi-level factors that influence overall implementation of a family-based intervention provided in schools and aimed at reaching the large child population with mental health service needs in Uganda. Moreover, the study draws upon an EBP that has already been tested for delivery by parent peers and community facilitators, and hence will take advantage of the advancing science behind task-shifting. If successful, the project has great potential to address global child mental health needs.

**Trial registration:**

ClinicalTrials.gov, ID: NCT03081195. Registered on 16 March 2017.

**Electronic supplementary material:**

The online version of this article (10.1186/s13063-018-2751-z) contains supplementary material, which is available to authorized users.

## Background

Currently, an estimated 450 million people, most of whom live in poverty and are from low- and middle-income countries (LMICs), experience serious mental health challenges [1]. Children in Sub-Saharan Africa (SSA) comprise half of the total regional population, yet current mental health services are severely under-equipped to meet their needs [1, 2]. A recent systematic review estimated that one in seven children in SSA may struggle with a serious mental health issue. The World Health Organization (WHO) estimates prevalence rates may be even higher (20%) [3]. Uganda (one of the poorest countries in SSA) reports 12 to 29% of children presenting mental health symptoms when screened in primary care clinics [4, 5] and found that one in five Ugandan adolescents evidences a serious mental health challenge. Given the large numbers of children in Uganda, child disruptive behavior disorders (DBDs), if untreated, are a particularly serious concern as they commonly persist through adolescence and adulthood [6–9].

DBDs are chronic, impairing, and costly mental health problems that, when left untreated, carry a high price resulting from disruptions in school performance, friendships, and family relations. DBDs impair academic and social functioning, disrupt the parent-child relationship, are associated with child maltreatment and abuse, and commonly co-occur alongside depression, anxiety, and substance use disorders. The impairment associated with DBDs in childhood also place youth at increased risk for future school dropout, substance use/abuse, delinquency, incarceration, criminal behaviors, and premature death [6–9]. Studies have identified specific risk factors for increased incidence of DBDs among children, including poverty, low parental educational attainment, maternal depression, harsh parenting, poor parent-child relationship, stress, and orphanhood (the death of one or both parents) [10–13]. Studies emphasize adverse outcomes associated with DBDs, including academic problems, social impairment, a higher incidence of chronic physical problems, unemployment and legal problems, and substance abuse and violence among adults [9, 14–20].

Six SSA countries, namely Uganda, Nigeria, South Africa, Ethiopia, the Democratic Republic of Congo, and Kenya have DBD prevalence rates, ranging from 12 to 33% [21–24]. Given the serious consequences of failing to intervene as DBDs emerge, it is imperative that effective and scalable solutions are discovered, while simultaneously recognizing the challenges facing these countries in meeting the educational and mental health care needs of their large youth populations. In Uganda, the focus of this paper, children make up about half (56%) of the total population (compared to 20% in the US) [25], and they most often present with multiple simultaneous physical, mental health, and educational challenges [25, 26]. Ugandan children live in disadvantaged communities with high rates of chronic poverty (38%), domestic violence (30%), physical violence toward children (80%), depression (33 to 39%), malaria (70 to 80%), and HIV or AIDS (6%) [27–32]. The country also has a significant number of orphans [9, 30]. Hence, for DBDs to be addressed, poverty and family economic capacities, family and community safety, as well as health and mental health co-morbidities must be taken into account in any evidence-based practice (EBP) considered for scale-up.

### Treatments for DBDs

The basic principles underlying effective parenting practices and child development are considered cross-culturally robust [33–37]. Positive behavioral supports, effective behavioral management, positive parent-child relationship, and parent involvement in a child’s life play critically important roles in the healthy development of all children, regardless of cultural or ethnic background. Many DBD focused EBPs are designed to enhance parenting skills [38–41] via behavioral practice, modeling, coaching, goal setting, family communication, and building on family strengths [41–45]. These components are embedded within the MFG model. Although MFG and other similarly effective interventions for the treatment of DBDs in youth have been tested in developed countries and in similar high-poverty and high-stress communities, and they are relevant for widespread dissemination in LMICs, most of these EBPs are widely not used in SSA countries.

### Rationale for applying 4Rs and 2Ss MFG intervention for DBDs

Kazdin and Whitley [46] describe how specific family factors tied to poverty (e.g., stress) may undermine parenting (e.g., family organization, discipline practices, family connectedness, support, communication) and contribute to serious childhood behavior problems [47–49]. In collaboration with parents and service providers in the US, this body of research was summarized to encourage transparency of the evidence base for families and to provide an “easy to remember” means of organizing existing science for family peer MFG facilitators [50–54]. Specifically, four broad conceptual categories were created and became the family level targets for MFG: Rules, Responsibility, Relationships and Respectful communication (4Rs). Stress and Social support (2Ss) were added as these impact service engagement and outcome. This same review of the evidence regarding the influence of parenting, quality of family life and youth behavioral challenges was also conducted in South Africa as part of the CHAMP (Collaborative HIV prevention and Adolescent Mental Health Project), an EBP listed on SAMHSA’s National Registry of Evidence-based Programs and Practices.

The MFG (guided by the 4Rs and 2Ss) involves six to eight families in the US and 12 to 20 families in South Africa [40, 55–63]. At least two generations of a family are present in each session. Content and practice activities foster both within-family and between-family learning and interaction [64]. The MFG targets primary school age children aged 7 up to 13 years in the US and South Africa. In the US, the MFG is designed for children struggling behaviorally and their families. In South Africa, MFG has targeted youth at high contextual risk for behavioral challenges (high rates of poverty, violence, family loss due to HIV and other health threats). In both countries, children and their families (including adult caregivers and siblings over 6 years of age) are invited to attend 16 sessions.

MFGs are also the core of SUUBI-Maka (Hope for families in Luganda), a family focused, economic-strengthening program tested in Uganda, [10–13, 65–71] furthering the evidence for their feasibility and acceptability in the specific context of this scale-up study. In addition, the development of MFG was guided by recommendations offered by Weisz [72] and Hoagwood [73] who argued that to improve implementation of EBPs, development and testing must occur in the setting where the service will ultimately be embedded, with the prior work in South Africa (SA) giving the MFG an important head start in learning about factors that influence implementation and scaling [40, 61, 70, 74, 75]. Also, both in the US and South Africa, MFGs have been facilitated by lay counselors or community health workers/village health teams, and parent peers, consistent with task-shifting strategies.

### Contextual influences on implementation and scale-up

Adapting EBPs to SSA countries requires thoughtful consideration of individual- and system-level factors [76–79]. Interventions developed in academic isolation too often fail to address the real-world constraints of settings in which they will be used – insufficient resources, limited workforce capacity, and failure to partner with funders and policy-makers [80]. In our previous work and in the current study, we draw upon PRISM (Practical, Robust Implementation, and Sustainability Model). PRISM is a practical and comprehensive implementation framework that integrates aspects of diffusion of innovation, models for quality improvement, and Reach-Effectiveness-Adoption-Implementation-Maintenance (RE-AIM). PRISM emphasizes: (1) organizational perspectives on an intervention (e.g., feasibility, adaptability, barriers); (2) external environment (e.g., community resources); (3) recipients’ characteristics (provider and parent response); (4) implementation and sustainability infrastructure (training and supervision supports); and (5) the RE-AIM approach to scaling. PRISM provides a framework to study the interaction of interventions with the characteristics of multi-level contexts/factors which may influence uptake, implementation, integration and youth outcomes (youth and adult caregiver response, provider preparedness, motivation and fidelity, community-level support). Figure 1 summarizes how site- (schools) and provider- (parent peers and community outreach health worker (CHW)-level variables may reflect key influences on implementation and ultimately child outcomes of MFG (not shown in this diagram is the contrast between the MFG and the comparison condition, which reflect the ultimate impact of the two MFG variants on child outcomes, these analyses will also be pursued). The delivery of MFG by parent peers versus CHWs is assumed to impact site (schools) and community-level interaction (path a) and provider-level influences (path b). Site and community-level interaction, in turn, affects provider-level (facilitators) variables (path c). These differential effects then carry through to the core family membes (path d), and in turn, child outcomes (path e).

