
### Aim 1. To examine short-term and longitudinal behavioral outcomes associated with the MFG

#### Hypothesis

Children who participate in MFG with their families will display significantly reduced conduct difficulties and increased functioning over time compared to those involved in the comparison condition. We expect that parent peers will evidence significantly more success engaging families to attend MFG sessions; thus, children in the MFG-parent-peer-delivered condition will evidence greater improvement relative to the other two study conditions.

We will consider a random-effects model for the child outcome variables across time as a function of treatment group, time and the interaction of group by time. A number of features will be common to all models. First, two levels of nesting will be explicitly modeled (caregiver and facilitator perspectives). At the third level of nesting, models may condition on a series of dummy codes capturing possible school-level effects. Second, the effect of primary interest is the test of the study condition (e.g., MFG-parent peer, MFG-community worker, comparison) by outcome trajectory (child behavioral symptoms and functioning) interaction. Third, time will be coded judiciously in accordance with a priori hypotheses about the time lags of effects of the experimental interventions. To adequately model hypothesized trajectories, higher-order polynomials can be estimated under different centering specifications, providing for multiple interpretations of the intercept and low-order trend components. Time contrasts can also be orthonormalized to reduce potential problems of multicollinearity in models specifying higher-order growth forms. Relevant trajectory variance components will also be evaluated to determine if there is variation (which would then be modeled as a function of both constant and time-varying covariates).

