### Aim 3. To elucidate multi-level factors that influence uptake, implementation, and youth outcomes

The overall analytic structure uses a three-level, multi-level SEM (MSEM) framework with family level variables at level 1, facilitator variables at level 2, and school variables at level 3. The analytic structure is complex, so we highlight our approach using Fig. 1 as our primary reference. We will employ mediation analysis with two-level MSEM models as explicated by Preacher, Zhang and Zyphur [119] and extended to three level models by Preacher [87]. We will use a combination of limited information estimation frameworks (focused on sub-portions of the full model) and full information estimation frameworks (focused on the entire three-level model) to strategically answer questions. At level 1, child outcomes are modeled as a function of the family predictors (see Fig. 1), taking into account the clustering at the higher levels of the model. The follow-up (6-month) measures of the mediators and the outcomes are included within the model in a classic SEM panel model with autoregressive effects, thereby linking the follow-up data to the immediate post-test data. This is an advantage of using MSEM over traditional multi-level modeling. Different centering strategies (e.g., grand mean vs. group mean) can be explored to garner various perspectives on the data. This feature of the model provides perspectives on the relative importance of paths in Fig. 1. To ascertain perspectives of the effects of school-level variables on facilitator variables, random intercept MSEM with the facilitator variables can be estimated as a function of the school variables that include dummy-coded treatment variables (MFG-parent peer vs. MFG-CHW) impacting the school mediators of readiness, leadership support and climate, which in turn, affect the facilitator-level intercepts. This modeling, or variants of it, address aim 3.

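### The Aim 3 model as described names no direct path from provider type to family variables or child outcomes, so indirect effects through site or facilitator variables can be biased, usually toward mediation

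*Protocol article*

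**What the plan says.** The section on contextual influences on implementation and scale-up describes Fig. 1 (not shown) as five paths. Delivery by parent peers rather than CHWs "is assumed to impact site (schools) and community-level interaction (path a) and provider-level influences (path b"). Then "Site and community-level interaction, in turn, affects provider-level (facilitators) variables (path c"). Last, "These differential effects then carry through to the core family membes (path d), and in turn, child outcomes (path e"). The same paragraph says what the diagram leaves out, namely the contrast of MFG with the comparison condition. It does not list a direct provider-type path among the omissions.

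The Aim 3 section takes Fig. 1 as its main reference. It states: "At level 1, child outcomes are modeled as a function of the family predictors (see Fig. 1), taking into account the clustering". Provider type enters as "dummy-coded treatment variables (MFG-parent peer vs. MFG-CHW) impacting the school mediators of readiness, leadership support and climate", and these mediators then act on facilitator intercepts. The section closes with "This modeling, or variants of it, address aim 3".

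Under quantitative data management and analyses, the plan expects many models to be over-identified. It lists global fit indices, residuals and modification indices, and allows the model to be revised where fit is poor.

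**The concern.** Aim 3 is meant to show which factors carry the difference between the two delivery modes. A model with no direct path presumes that the named site and facilitator variables carry all of it. The protocol gives reason to expect other routes: the Aim 1 hypothesis is that "parent peers will evidence significantly more success engaging families to attend MFG sessions", and this could come from being a neighbour or fellow parent as well as from anything measured on facilitators or school climate.

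Schools are randomised, so provider type is constant within a school and its indirect effect can rest only on between-school relations. In those relations provider type is a common cause of mediator and outcome unless it is in the outcome equation. What is at stake is the naming of a mechanism: a site or facilitator variable with no effect of its own could be reported as the reason one delivery mode did better.

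**Working it through.** The article gives no figure to reproduce here, so the check has two parts: the paths as written, and the size of the bias if a direct path exists but is left out.

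**1. Paths as written.** Provider type to site (a); provider type to facilitator (b); site to facilitator (c); these effects to family (d); family to child (e). The Aim 3 text has child outcomes on family predictors, and provider dummies on school mediators that lead to facilitator intercepts. The two accounts agree, and neither names provider type to family or provider type to child.

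**2. Algebra.** Let X be provider type (±0.5, so variance 0.25), M a mediator with M = dX + error of variance v, and Y a downstream variable with mediator slope β and direct effect c'. If the direct path is fixed at zero, the fitted slope tends to β + c'·cov(X,M)/var(M). Multiplying by d gives the fitted indirect effect:

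dβ + c'·R², with R² = 0.25d² / (0.25d² + v).

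So a fraction R² of the direct effect is counted as mediation. R² is the share of mediator variance explained by provider type.

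- With v = 1: d = 0 gives 0%; d = 0.5 gives 0.0625/1.0625 = 5.9%; d = 1 gives 0.25/1.25 = 20%; d = 2 gives 1/2 = 50%. With only 20 schools, simulation gives about 10%, 24% and 52% for d = 0.5, 1 and 2.
- With a facilitator variable averaged over six facilitators, assuming facilitator variance 1 and school SD 0.2: v = 0.04 + 1/6 = 0.207. Then d = 0.5 gives 0.0625/0.269 = 23%, and d = 1 gives 0.25/0.457 = 55%. Simulation with 20 schools gives about 27% and 58%.

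**3. False mediator findings.** Inputs from the protocol: 10 versus 10 schools; about six facilitators per school; 1000 dyads per condition, so 1000/10 = 100 per school and 100/6 ≈ 17 per facilitator. Assumed: school SD 0.2 for mediator and outcome, true mediator effect zero, two-sided 5% test, regression on school means, 4,000 trials per setting. The table shows how often the null mediator path is significant.

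| Mediator shift | Provider type left out, direct effect 0.2 / 0.3 / 0.4 SD | Provider type included |
|---|---|---|
| 1 SD | 28% / 51% / 70% | about 5% |
| 0.5 SD | 15% / 22% / 31% | about 5% |

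The rates fall if the mediator itself varies more between schools. At the smallest direct effect they drop to about 15% (1 SD shift) and 7% (0.5 SD shift), and further if that variation is larger still. A random-intercept fit at facilitator level, which draws mostly on within-school variation, showed no material bias.

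**4. Would a test of the omitted path catch it?** In the table's setting with a 1 SD shift, a direct test of provider type had power of about 23%, 46% and 67% for direct effects of 0.2, 0.3 and 0.4 SD. With school-level residual SD 1 and a 1 SD shift, power was about 15%, 43% and 79% for direct effects of 0.5, 1.0 and 1.5 school-level SD.

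**The case against.** The strongest reply is that a condensed, conceptual account is being read as a closed specification. Fig. 1 is not available, the prose presents it as a summary of possible influences, and the Aim 3 section speaks of models that can be estimated and ends by allowing variants. This stands in part. A reader might infer that the fitted model is certain to fix the direct path at zero, and the documents do not establish that. They do show that the only model described lacks the path, and allowing variants does not commit the analysis to including it.

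A second reply is that over-identified models are tested, so residuals and modification indices could reveal a missing path. This is right in principle; the plan does have a check. But it would add the path only after misfit had been seen, and step 4 shows how uneven its power is with 10 schools per delivery mode.

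Third, a direct effect of 0.2 to 0.4 SD equals 1 to 2 of the assumed school SDs (0.2/0.2 to 0.4/0.2), which is large for two active arms. The calculation is also a single-mediator regression on school means, not the three-level MSEM. Both points stand, so the rates are illustrations and not forecasts for this trial.

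Fourth, better engagement by peers may itself run through facilitator variables to families (paths b, d and e), so the Aim 1 hypothesis does not contradict the model. That also stands. The hypothesis makes another route plausible and does not prove one. Aim 1 tests the total effect of condition without mediators, but it cannot divide that effect into direct and indirect parts.

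**Conclusion.** The point holds for the model as described. No direct path from provider type to family or child is named, and any such path is left to diagnostics after fitting. If a direct effect exists and provider type also moves the mediator, the indirect effect is shifted by c'·R². It is overstated when the direct and true indirect effects have the same sign, and offset when they differ. Under the assumptions above, the absorbed share with 20 schools is about 10% to 27% for a 0.5 SD mediator shift and 24% to 58% for a 1 SD shift.

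Two stronger readings are not supported. A reader might infer that every other peer-versus-CHW difference would be reported as mediation. Only the share R² is absorbed, it is zero where provider type does not move the mediator, and the rest appears as misfit or residual. A reader might also infer that the model bars site variables from acting on families. The sentence introducing path d follows statements about both site and provider effects, so it can include them. Purely within-school paths are not affected, and the Aim 1 test of condition is untouched.

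**What to change.** In the Aim 3 MSEM, include by default direct paths from the provider-type dummy to the family variables and to the child outcomes. Take the indirect effects from that model and report the direct effect with its interval beside them. Keep the five-path model of Fig. 1 as a nested restriction to be tested against the fuller model, not as the starting model to be relaxed if fit is poor.

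The cost is a few extra parameters and wider intervals for the school-level paths, which will be noticeable with 20 schools. Only the analysis wording changes; design, sample and data collection stay as they are.
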